## Abstract

Physical exercise has shown positive effects on symptomatology and on the reduction of comorbidities in population with autism spectrum disorder (ASD). However, there is still no consensus about the most appropriate exercise intervention model for children with ASD. The physical exercise program for children with autism (PEP-Aut) protocol designed allow us to (i) examine the multivariate associations between ASD symptoms, metabolic profile, physical activity level, physical fitness, and health-related quality of life of children with ASD; (ii) assess the effects of a 40-week exercise program on all these aspects of children with ASD. The impact of the exercise program will be assessed based on the sequence of the two phases. Phase 1 is a 12-week cross-sectional study assessing the symptomatology, metabolic profile, physical fitness and physical activity levels, socioeconomic status profile, and health-related quality of life of participants. This phase is the baseline of the following phase. Phase 2 is a 48-week intervention study with a 40-week intervention with exercise that will take place in a specialized center for children with ASD in the city of Maceió-Alagoas, Brazil. The primary outcomes will be change in the symptomatic profile and the level of physical activity of children. Secondary outcomes will be anthropometric and metabolic profiles, aerobic function, grip strength, socioeconomic status, and health-related quality of life. The study will provide critical information on the efficacy of exercise for children with ASD and help guide design and delivery of future programs.

## Introduction

Autism spectrum disorder (ASD) refers to a complex category of the neurobiological development disorders, which is typically diagnosed during childhood (1). The main symptomatological characteristics are (a) persistent deficits in social communication and social interaction and (b) restricted, repetitive patterns of behavior, interests, or activities. Symptoms may present in three levels of intensity that is directly related to the necessary support: level 3 requiring very substantial support, level 2 requiring substantial support, and level 1 requiring support in the main areas of symptomatic ASD (2).

Estimates of the prevalence of ASD are scarce (3, 4) possibly due to the complexity of the symptoms and comorbidities associated with the disorder (5). To the best of our knowledge, the only study carried out in Brazil on the prevalence of ASD (6) showed that prevalence was almost 0.3% in school age children, much lower than figures reported in most other surveys (7). The majority were males (80%) confirming the 4:1 male/female ratio reported (8, 9) and born from older mothers (50%), consistent with recent studies documenting parental age as a risk factor for autism (10).

In addition to studies aiming to reduce the symptomatic effects (11), attention has been paid to the health of the child with ASD (5, 12, 13). Several studies have suggested that children with ASD present greater health problems when compared to children with normative development (14, 15). There is evidence that children with ASD have higher risk of comorbidities (15, 16), sleep disturbance (17, 18), metabolic disorders (19), hyperactivity (20, 21), motor activity disorders (22), obesity (23–26), and lower health-related quality of life for children and their families (5, 12).

Autism spectrum disorder symptomatological characteristics cause significant interference in physical activity (PA) patterns (27, 28). Deficits in social communication are barriers that limit access to sports in school and to free time playing experiences after school (29–31). Also restricted and repetitive patterns of behavior limit an individual’s interaction with the environmental context because this pattern is involuntary, with an exclusive function of producing physical and sensorial self-regulation (32).

It is more likely that children with ASD show higher deficits in motor abilities when compared to children without ASD. There is evidence showing that motor deficits in children with ASD are characterized by balance, postural stability, coordination deficits, and presence of motor dyspraxia (22). Children with ASD are less active than children without ASD, observed when comparing time of moderate and vigorous physical activities (33–35). Thus, children with ASD are more vulnerable to overweight and obesity (33, 36–38).

Interventions have been conducted to reduce ASD symptoms (11) and comorbidities (12, 13). Physical exercise (PE) as a treatment, for example, started in the early 1970s and showed positive effects on aquatic skills and social interaction learning (39). Currently, systematic reviews (40, 41) and meta-analyses (42, 43) have shown positive effects for PE on both symptoms and comorbidities related to the disorder with the strongest evidence for symptom improvement when compared to improvements in the individual’s overall health (44).

Among the positive effects reported as a result of PE are a reduction in stereotyped (45, 46) and aggressive behavior (45) and a decrease in body mass index (BMI) in children with ASD (47). In addition, improvements have been seen in motor coordination, dynamic equilibrium (22, 48), manual muscle strength (49), academic performance (45, 47), and different psychosocial domains (50). Detailed information provided in these papers on the specifics of exercise interventions for children with ASD, such as exercise intensity, volume, and frequency, has largely been absent (41). Unfortunately, this has made replication difficult, and the identification of effective exercise components has not been possible (42). Walking and running programs are the most common modes of delivery (47, 51–53), followed by water-based activities (39, 49, 54–56). Few studies have reported the intensity of PE (44). Two studies reported attempts to control exercise intensity to a range of 50–60% of the predicted maximum heart rate (PMHR) with a progressive increase to 70–80% of PMHR (54, 57). The length of the PE interventions has ranged from 8 to 36 weeks, with a session frequency of two to three times per week and a session duration of 20–40 min (44).

There is also limited description of any special adaptations used in the program for individuals with ASD (41, 42, 46) since it is possible that they do not process exercise in the same way as in individuals without ASD (44).

In the existing literature, there is a shortage of specific information such as age (58–60) and diagnostic variations of the participants (49, 54, 57, 61) making comparison between studies less meaningful. From a research perspective, insufficient details on the preintervention and postintervention evaluation procedures (41, 42, 46) or the measurement instruments used (39, 51, 52) are provided to allow replication.

Therefore, there is the need for an intervention study with a design that specifies the characteristics of the exercise program, the adaptation procedures, the different intervention phases, and the type of assessment used, so that a closer understanding of the specific effects of exercise on symptoms and comorbidities can be achieved.

## Aims of the Study

(a)To examine the multivariate associations among ASD symptoms, metabolic profile, PA level, physical fitness, and health-related quality of life of children with ASDs.(b)To assess the effects of a 40-week exercise program on the metabolic profile, PA level, physical fitness, and health-related quality of life of children with ASD.

## Initial Procedures

### SEC-Aut Eligibility Criteria

During the last decades, the WHO has increasingly recognized the role of exercise and PA and its impact on health and well-being, including individuals with disabilities. Thus, institutions, families, and caregivers are particularly receptive to participate in exercise intervention programs, particularly in social contexts and communities where the offer for such services is scarce or inexistent. Four specialized education centers (SEC-Aut) in the city of Maceió, Alagoas-Brazil, will be formally contacted to confirm their expressed interest and availability to potentially participate in this study and create the singular conditions required for its implementation with children with ASD. From the four SEC-Aut’s assessed, only one will be selected to take part in the study to ensure that all children with ASD participating in PEP-Aut are experiencing the same attendance procedures, type of intervention, weekly training volume, and the same type of exercise setting. The three excluded SEC-Aut’s will alternatively participate in 4-month recreational and sociocultural activities program (1 day per week) offered by a member of the research team at the Department of Physical Education of the Federal University of Alagoas, Brazil. The SEC-Aut will be selected using the following eligibility criteria: (i) availability to participate in all phases of the study during a total period of 22 months; (ii) potential for signing up the largest number of participants eligible for the study; (iii) existence of an indoor and outdoor area with appropriate conditions to implement PEP-Aut sessions; (iv) adequate professional and family support to implement and monitor the PEP-Aut sessions in children with ASD; and (v) willingness to work with the research team on adjustments and improvements in the intervention protocol.

An information session will take place in the selected SEC-Aut, where participants and their parents and legal representatives will be informed about the study’s specific objectives, data collection procedures, and characteristics of the intervention program. This study will follow the recommendations of ethical guidelines for research with human beings (62) and the Brazilian Health Council Resolution, number 466 of December 12, 2012, with written informed consent from all subjects (63). Written consent was obtained from the participants and their parents in accordance with the Declaration of Helsinki (64). The protocol was approved by the Federal University of Alagoas Ethical Committee (Reference number: 1.091.864).

### Participants with ASD Eligibility Criteria

The eligibility criteria for ASD participants include the following: (i) to have a certified medical diagnosis of Asperger’s syndrome, autism, or developmental disorder without specification, in accordance with the standards established in the Diagnostic and Statistical Manual of Mental Disorders, fifth edition (DSM-5) (1); (ii) to present a recent history of non-participation in PE programs or similar physical motor activities; (iii) initial medical checkup to determine fitness to participate in PE program; and (iv) the absence of other syndromes and motor impairment conditions associated with ASD.

**Figure 1 F1:**
[figure not shown]
Timeline of the PEP-Aut’s phases (cross-sectional and intervention).

## Estimated Sample Size

The variable “occurrence of stereotyped behaviors” will be the primary outcome of this study. We will calculate the total sample from the power associated with the effect size and the difference of the means from the overall effect size of the results from similar studies that test the effectiveness of the PE programs in children’s stereotyped behaviors, clinically diagnosed with ASD (Cohen’s d effect size = 1.41) (45, 52, 53, 60).

To detect possible differences between the means of the primary measure with a power of 80% (*n* = 0.05), 39 children would be necessary to verify a positive effect of the PE program on the stereotyped behaviors of this population. In addition to these children, and aiming to prevent possible losses estimated as 30% characteristic from longitudinal PE programs, 12 participants will be added to the initial sample, and totally 51 individuals will be selected for the study (65).

For the Phase 1 cross-sectional study, it is possible to assess at least 145 participants from both sexes, with age ranging from 4 to 12 years, following a procedure reported in recent studies (40, 43).

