## Outcome Measures

All outcome measures will be collected two times: (a) in Phase 1 (cross-sectional study, weeks 1–12) and (b) in Phase 2 (intervention study, between weeks 13–16 and 57–60). Primary outcomes are related to the symptoms profile and the level of PA. Secondary outcomes will be the metabolic profile, the anthropometric measurements, the functional level, the handgrip strength, the socioeconomic status, and the health-related quality of life. A characteristic of this study is that some of the measurements are applied to participants families or legal representatives (Socio-economic Questionnaire, Child Health Questionnaire, SAT, and CATS), while others are applied to the participants with ASD themselves (PA level, anthropometric measures, aerobic function, hand-grip strength, and blood collection).

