### Childhood Autism Rating Scale

Childhood Autism Rating Scale is a standardized instrument to identify levels of intensity of ASDs (mild, moderate, and severe), as well as the sharp distinction between autism and intellectual disability (69). The instrument is based on the diagnostic criteria of Kanner (70), Creak (71), Rutter (72), Ritvo and Freeman (73), and DSM, third edition (DSM-III). The Brazilian Portuguese version of this instrument (CARS-BR) (69) will be used to evaluate the child’s behavior from 14 domains that are usually affected by serious problems in autism, plus a general category of autism impressions. The aim of the instrument is to identify children with ASD and differentiate them from children with other developmental disorders. The 15 items of the scale are relative to people, imitative behavior, emotional response, body use, use of object, adaptation to change, visual response, auditory response, perceptual response, fear or anxiety, verbal communication, non-verbal communication, activity level, level and consistency of intellectual relations, and general impressions. The score ranges from 1 to 4 for each item: 1 indicates adequate behavior for the age level, while 4 indicates severe deviation from normal behavior for the age level. The scores of the individual items are summed in a total score, which rates the child as non-autistic (below 30), mildly or moderately autistic (30–36.5), or severely autistic (above 36.5). It is also necessary to count the number of items in which the child scored at or above 3. A diagnosis of severe autism is appropriate if these items are at least 5. A score of 30 or more is used as the threshold value for diagnosis of autism.

The validation process was attended by 60 patients and, in terms of validity, demonstrated a very good internal consistency, with mean values of Cronbach’s alpha coefficient of 0.82 (95% CI, 0.71–0.88), indicating a high degree of internal consistency (69, 74). Data on the convergent validity, compared to the Autistic Traits Assessment Scale, showed Pearson’s correlation coefficient values with *r* = 0.89. The test–retest reliability had a kappa coefficient value of 0.90.

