### Scale of Autistic Traits

The SAT is an instrument that allows a first identification of the symptoms profile of ASDs (75). In its original construction, the diagnostic criteria of DSM-III, DSM-III-R, and ICD-10 were considered to develop the instrument. The ATA scale is an easy-to-apply instrument, accessible to professionals who have direct contact with the autistic population (e.g., teachers or even parents) informing the current state of the patient. The instrument was developed to be used by professionals, not necessarily medical doctors, responsible for the evaluation of the answers according to each item. It is not, therefore, a diagnostic interview, but a standardized test that gives the cognitive behavioral profile of the child with ASD. The scale score is based on the following criteria: (i) each subscale of the test has a value from 0 to 2; (ii) the positive scale is scored when one of the items is positive; (iii) the overall scale score is based on the arithmetic sum of all the positive values of the subscale, allowing a very precise characterization of autism.

The Brazilian Portuguese translation and validation considered corrections of the diagnostic criteria, resulting from the publication of the DSM-IV (76). The cutoff point was 15 (*p* ≤ 0.05); the coefficient of variation (reliability) was 0.27, and the external validity showed low agreement (kappa = 0.04). Finally, the internal validity was 100%, showing that the clinical diagnoses agreed with the results obtained by applying the scale. The correlation value obtained was 0.42, being specific for the autistic conditions. It also presented good internal consistency, with Cronbach’s alpha 0.71. Thus, the scale is considered to be adequate and reliable for us to use in our applied educational context, with children and young people involved in PE.

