Validation of the multilevel models will be made by visual inspection of plots of residuals versus predicted values from the analyses. Considering available data, full maximum likelihood or restricted maximum likelihood estimations will be explored to obtain the unknown parameters. Likelihood ratio test and Akaike’s Information Criterion (AIC) will be considered for model comparisons. Multilevel models will be mostly derived using “nlme” package (97), within the R statistical language (98).

Qualitative data will be collected using a semistructured interview research format. A script of interview questions will be developed containing the thematic topics to be addressed throughout the interview, from a retrospective temporal analysis perspective as well as some key issues, i.e., the interview guide questions were inductively generated and reflected thinking, feeling, and knowing questions (99). After obtaining ethical approval, children with ASD parents and legal representatives will be invited to voluntarily agree to take part in the research, aiming to obtain a deeper understanding of their feelings, beliefs, ideas, and opinions about the effects of PEP-Aut participation in children behavior and particularly in the occurrence of stereotyped behaviors.

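### The trial is sized on stereotyped behaviours as its sole primary outcome, but other sections name two different primaries and no score is designated to measure stereotypy

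*Protocol article*

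**What the plan says.** All references are to the protocol article.

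- **Estimated Sample Size** names one outcome: "The variable “occurrence of stereotyped behaviors” will be the primary outcome of this study". The effect size, Cohen's d = 1.41, is taken from studies of exercise and stereotyped behaviours. The section asks for 39 children at 80% power, raised to 51 for losses.
- **Outcome Measures** names two: "Primary outcomes are related to the symptoms profile and the level of PA".
- **Abstract** agrees with Outcome Measures: "The primary outcomes will be change in the symptomatic profile and the level of physical activity of children".
- **Aims of the Study**, aim (b), is "To assess the effects of a 40-week exercise program on the metabolic profile, PA level, physical fitness, and health-related quality of life". It mentions neither symptoms nor stereotypy. The Abstract's second aim refers back to a list that does include ASD symptoms.
- **Instruments.** CARS is listed item by item ("The 15 items of the scale are relative to people, imitative behavior, emotional response, body use, use of object", and so on) and summed to a total. SAT is described only by its scoring: "the overall scale score is based on the arithmetic sum of all the positive values of the subscale". The other measures are a socioeconomic questionnaire, the Child Health Questionnaire, accelerometry, anthropometry, a run/walk test, grip strength and blood tests.
- **Data Analysis** describes parent interviews about the effects of the programme, "particularly in the occurrence of stereotyped behaviors".
- **Discussion** treats incidence of stereotypies as the symptom effect of interest and expects their number to fall.

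**The concern.** A reader cannot tell which result decides the trial. One section makes it a single stereotypy variable, two sections make it symptoms together with PA, and the aim that should carry the intervention question names PA but not symptoms. These statements cannot all hold, and an analysis plan could settle the matter only by overriding one of them.

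The power statement has the same difficulty. It is built on an effect reported for stereotypy, yet none of the described instruments is linked to that variable. The interviews collect parents' opinions and cannot supply the difference in means that the calculation refers to. PA, named as a primary outcome twice, has no effect size anywhere in the article. If this stays open, the primary outcome could be chosen after the results are seen, and a positive finding on either symptoms or PA could be presented as the main result.

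**Working it through.** **Step 1. The sections side by side.**

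| Section | Primary outcome or aim | Stereotypy | Symptoms | PA |
|---|---|---|---|---|
| Abstract | two primaries | not named | yes | yes |
| Aims, aim (b) | intervention aim | not named | not named | yes |
| Estimated Sample Size | one primary | yes | not named | not named |
| Outcome Measures | two primaries | not named | yes | yes |

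No two of these three sections agree: Aims, Estimated Sample Size and Outcome Measures. Only the Abstract and Outcome Measures match on the primaries.

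**Step 2. Is stereotypy tied to a score?** None of the 15 CARS items is labelled stereotypy, and the scale is used as a total. The SAT items are not listed, and only an overall sum is described. No other instrument is linked to stereotypy. The sole planned data collection that names it is the interview.

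**Step 3. The plan's own sample size.** Inputs from Estimated Sample Size: d = 1.41, power 80%, 0.05 (printed as n, read here as alpha). Assumed: two-sided test, 1:1 allocation.

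- Normal formula, per arm: 2 × (1.960 + 0.842)² / 1.41² = 7.9, so 8 per arm and 16 in total.
- t-test: 8.97, so 9 per arm and 18 in total.
- One-sided tests give 14 to 16 in total. Allocation ratios of 2:1 to 4:1 give 18 to 25.

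None of these gives 39. With 39 in total, power at d = 1.41 is about 99%. The 51 is 39 × 1.30 = 50.7. The origin of 39 is a separate question, but the figure cannot be read as sizing some other endpoint, because no other effect size is given.

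**Step 4. What the planned numbers can detect on any one variable** (t-test, 1:1, two-sided 0.05, 80% power):

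| Children analysed | Detectable standardised difference |
|---|---|
| 36 (51 less 30%: 51 × 0.70 = 35.7) | 0.96 |
| 39 | 0.92 |
| 51 (no losses) | 0.80 |

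The article gives no effect size for PA, SAT or CARS. As an assumed range, 39 children give about 68% power at d = 0.8 and about 33% at d = 0.5.

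**Step 5. Two primaries at 0.05 each.** For independent tests, 1 − 0.95² = 9.75%. Positive correlation between symptoms and PA would lower this.

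**The case against.** The best defence is that the conflict on the symptom side is only partial. The Discussion presents incidence of stereotypies as the symptom effect, so the sample-size variable may be meant as the symptom outcome, or part of it. Aim (b) may simply have lost a word, since the Abstract's version covers symptoms. A journal article also condenses, and testing order is commonly left to an analysis plan. This narrows the point but does not remove it. Which variable is primary is stated differently in sections of one document, no score is designated, and PA stands as a second primary that the sizing ignores.

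Four stronger readings are tempting, and the article does not support them.

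- **That stereotypy is not collected at all.** The SAT items are not listed, and the section on type of mediation uses SAT variables that the SAT section never mentions. CARS has items on body use and object use, which overlap with the stereotyped movements described under the PEP-Aut exercises. What can be said is that no score is designated.
- **That three primary tests (SAT, CARS, PA) give 14.3% family-wise error.** That figure, 1 − 0.95³, assumes independence. The CARS section reports r = 0.89 with the Autistic Traits Assessment Scale, and the SAT section calls its instrument the ATA scale. If the two test statistics correlated at 0.89 and PA were independent, the figure would be about 11.8%. The article also does not state that three such tests are planned.
- **That SAT is shown to be the weaker scale.** The kappa of 0.04 for SAT concerns external validity and the 0.90 for CARS concerns test–retest reliability. These are different properties.
- **That the CARS total must be the primary.** It is presented as an instrument for identifying and grading autism, no data on responsiveness are given, and adopting it would give up the basis for d = 1.41. The choice of score belongs to the sponsor.

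**Conclusion.** The point holds as an internal contradiction. The article fixes no single primary endpoint: the outcome used for sizing differs from the two primaries named in the Abstract and Outcome Measures, and it is assigned to no score. The stated 80% power therefore belongs to no identified quantitative endpoint and does not extend to PA. Treating symptoms and PA as two primaries at 0.05 each would give about 9.75% family-wise error. That figure rests on independent tests and on each being tested separately, which the article does not spell out. The contradiction itself rests on no assumption. The detectable differences in the working assume a two-sided t-test at 0.05 with equal arms. The matter must be settled before outcome data are examined.

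**What to change.** - **Primary variable.** Name one stereotypy or symptom score from the instruments already in the battery (an item set, subscale or total), measured at weeks 57–60 and adjusted for baseline. Use the same wording in the Abstract, Aims, Estimated Sample Size and Outcome Measures.
- **PA.** Make it secondary, or place it second in a stated testing order.
- **Aim (b).** Add symptoms, in line with the Abstract.
- **Sample size.** Restate the sentence as the standardised difference detectable on the named score with the planned number of children. Under the assumptions above, that is about 0.92 with 39 analysed. Keep d = 1.41 only if it is justified for that score.

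No new measurement is needed. The cost is that PA loses equal primary status, and the power statement may look less favourable if 1.41 does not carry over to the chosen score.

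### The 30% loss allowance is taken on the 39 children needed, not on those enrolled, so 51 covers a 23.5% loss and a 30% loss leaves about 36

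*Protocol article*

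**What the plan says.** All the figures stand in the protocol article, section Estimated Sample Size.

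- Planning effect: "Cohen’s d effect size = 1.41", taken from similar studies of stereotyped behaviours.
- Error rates: "with a power of 80% (*n* = 0.05". The 0.05 is printed with the letter n and is read here as the significance level.
- Number required: "39 children would be necessary to verify a positive effect of the PE program".
- Loss allowance: "aiming to prevent possible losses estimated as 30% characteristic from longitudinal PE programs, 12 participants will be added to the initial sample".
- Total: "totally 51 individuals will be selected for the study".

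No other section gives a different loss rate or another reason for adding 12. Methods/Design specifies simple randomization into an exercise and a control group and does not state the ratio.

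**The concern.** An allowance for losses exists so that the required number is still there at the end. Here the percentage was applied to the required number and the result added on. A loss rate acts on everyone who enters, including the extra children, so adding 30% of the target does not offset a 30% loss. The section therefore promises protection that its own figures do not give.

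The allowance is not a formality in this trial. The exercise program runs for 40 weeks and 80 sessions. The section Program Attendance/Adherence says that earlier studies gave no guidance on adherence, and it plans an attendance cutoff for inclusion in the final statistics. That cutoff could reduce the analysed number further. The intervention also draws on a single center, so late replacement may be difficult. A reader who takes 51 as safe against a 30% loss would be misled about the margin.

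**Working it through.** **Inputs** (Estimated Sample Size): required number 39, loss rate 30%, number added 12, total 51, d = 1.41, power 80%, significance level 0.05.

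**Step 1. Reproduce the plan's figure.**
- 39 × 0.30 = 11.7, rounded up to 12.
- 39 + 12 = 51; equivalently 39 × 1.30 = 50.7, rounded up to 51.

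The stated total is reproduced exactly by multiplying by (1 + loss rate).

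**Step 2. Apply the stated loss rate to those enrolled.**
- 51 × (1 − 0.30) = 35.7, about 36 (35 if rounded down).
- Shortfall against 39: 3 children (4 if rounded down).

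**Step 3. Find the loss that 51 can absorb.**
- (51 − 39)/51 = 12/51 = 23.5%.

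**Step 4. Find the enrolment that keeps 39 at a 30% loss.**
- 39/(1 − 0.30) = 39/0.70 = 55.7, rounded up to 56, which is 17 added and not 12.
- Check: 56 × 0.70 = 39.2.

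**Step 5. Size the consequence for power.** Assumptions: two-sample t-test, two-sided 0.05, equal arms. The article states neither the sidedness nor the allocation ratio, and its planned analysis is a two-level growth model, so these are approximations.

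| Total analysed | Power at d = 1.41 (stated) | Power at d of about 0.92 (back-solved) |
|---|---|---|
| 39 | about 99% | about 80% |
| 36 | about 98% | about 77% |
| 35 | about 98% | about 75% |

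The value 0.92 is not in the article. It is the effect for which 39 children in total would give 80% power, found by solving backwards. At the stated d = 1.41, 80% power needs about 9 per arm, or 18 in total, so 39 does not follow from the section's own inputs.

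**The case against.** The best defence of the text is that 30% was meant as a share of the 39, so that 12 children are expected to be lost and 12 are added. That makes the sum internally consistent. But the section describes the 30% as typical of longitudinal exercise programs, which is a rate among participants. A loss of 12 at that rate would come from 12/0.30 = 40 children, not 51. The defence does not stand.

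The stronger objection concerns consequence. A reader might infer that the trial will miss its 80% power because it ends with 36 children. The article does not support that. Its only stated effect is d = 1.41, for which 36 children give about 98% power under the assumptions above. Power falls below 80% only if 39 is taken as the true 80% requirement. That implies d of about 0.92, a value which appears nowhere in the article and conflicts with the one that does. This objection stands, and it limits the point to the arithmetic of the allowance.

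It is also fair to say that the sidedness, the allocation ratio and the growth model leave the power figures approximate. Steps 1 to 4 depend on none of these.

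**Conclusion.** The allowance is wrong as written. On the article's own figures, 51 enrolled children protect the target of 39 against a 23.5% loss, not 30%. At 30%, about 36 remain, 3 short. This needs no assumption beyond reading the 30% as a loss rate among those enrolled.

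The issue is minor in size. It does not show an underpowered trial at the stated effect. The drop to about 75–77% power is conditional on an effect of about 0.92, which is an assumption of this check and not a planning value of the trial. That 39 cannot be obtained from d = 1.41 and 80% power is a separate matter in the same section. Until it is settled, how much the shortfall of 3 children matters cannot be stated more firmly.

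**What to change.** In Estimated Sample Size, replace the sentence on losses with wording to this effect, leaving enrolment as it is:

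> Enrolling 51 children allows for a loss of 23.5% while retaining 39. With a loss of 30%, about 36 children would remain. Retaining 39 at a 30% loss would correspond to 56 enrolled.

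Do not add a revised detectable difference (for example 0.96 SD, the 80% figure for 18 per arm) at this stage. Beside an unreconciled d = 1.41 it would put two incompatible planning effects in one section. The basis for 39 should be reconciled with d = 1.41 first.

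The cost is wording only. The stated tolerance for losses becomes less favourable, and nothing in recruitment or conduct changes unless the sponsor chooses to enrol towards 56.
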